### Withdrawal

Participants are free to withdraw from the trial at any time, without this affecting their care, by informing a member of the research team. Participants who withdraw will not be replaced, and data already collected will be used unless the participant requests that it be removed.

Participants might choose not to attend the commercial weight loss programme, or may stop attending sessions during the trial. Participants who withdraw from the intervention will be followed up at assessment appointments in the same way as other participants unless they also choose to withdraw from the trial.

Three contact attempts (by different means and at different times) will be made for each follow up appointment. On the third attempt to schedule an appointment, or where a participant informs us that they are unable or unwilling to attend a follow up appointment, a self-measured weight will be requested. These data will not be included in the primary analyses but will provide additional data that can be used for sensitivity analyses where it is considered appropriate.

### Interventions

#### Referral to a commercial provider

Participants who are assigned to the two commercial referral arms will receive vouchers to attend Weight Watchers sessions and asked to attend a local meeting that is convenient for them. They will be asked not to mention their participation in the trial to the group leader or other members, to make their experience as representative as possible.

**CP12:** Participants allocated to the 12 week referral will receive free vouchers to attend 12 Weight Watchers sessions and access to their internet resources for 16 weeks. This is the package currently used in the WW NHS Referral Scheme and currently costs the NHS £55 + VAT.

**CP52:** Participants allocated to the 52 week referral will receive free vouchers to attend 52 sessions of Weight Watchers and access to their internet resources for 12 months. This packages is estimated to cost the NHS £190 + VAT.

### Brief intervention

The control intervention is a standardised brief intervention: recognition of the problem by the GP (letter of invitation), basic written information on self-help weight loss strategies provided by a member of the research team at the baseline visit (British Heart Foundation Booklet: So you want to lose weight… for good) and weighing at follow up (coincides with outcome measurements at 3, 12 and 24 months).

### Adherence

Attendance at CP meetings will be monitored both through self-report at assessment appointments and data collected by WW at weekly meetings (which can be provided, with consent, through the WW NHS referral database and tracked using NHS referral ID) and these data will be controlled for in sensitivity analyses. Similar information may be available from WW regarding website usage, and this data will be combined with that collected via self-report. We will also collect self-report data on the extent to which BI participants have used their self-help materials.

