### Clinical effectiveness

The primary analyses will assess differences in mean weight change from baseline to 12 months between the intervention groups. In order to investigate the impact of missing data, four analysis approaches will be taken: completers only, baseline observation carried forward (BOCF), last observation carried forward (LOCF) and a missing at random (MAR) analysis using a variance components model. For the LOCF, BOCF and completers analyses, fixed effect models for continuous normal data will be fitted to the 12 month weight data. The fixed effects will be intervention group, centre and baseline weight. For the MAR analysis, a model for multivariate normal data with the same fixed effects will be fitted using measured weights at each time point using generalised least squares. Coefficient estimates and their 95% confidence intervals will be calculated for each fixed effect.

All assumptions of the models will be checked using appropriate graphs (eq a Q-Q plot of residuals to check normality, residuals versus predicted values to check homogeneity of residual variance.) If the residuals are not normally distributed then the dependent variable may be transformed to normality, if there is no such transformation then non-parametric methods will be considered.

Secondary analyses will include analyses of weight change at 3 and 24 months; changes in blood pressure, waist circumference and fat mass at 3, 12 and 24 months; changes in biochemical measures at 12 months. These will be analysed using the same regression based models. Numbers of participants in each group achieving ≥5% and ≥10% weight loss at 12 and 24 months will also be explored.

Summary tables will be produced to look at the demographic distribution of the sample (age, sex, initial weight, BMI); attendance rates; time course of attendance; website usage.

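### Controlling for programme attendance in the between-arm sensitivity analyses conditions on a mediator and can distort the arm differences, so it cannot test the intention-to-treat result

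*Protocol article*

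**What the plan says.** The Adherence section of the protocol article describes the data source: "Attendance at CP meetings will be monitored both through self-report at assessment appointments and data collected by WW at weekly meetings". It then commits, without qualification, that "these data will be controlled for in sensitivity analyses". It does not say whether attendance enters as a count, as a share of the sessions offered or as a yes/no variable. Nor does it say what value BI participants take or which comparison is meant.

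The Interventions section sets the entitlement by arm. CP12 participants "will receive free vouchers to attend 12 Weight Watchers sessions"; CP52 participants "will receive free vouchers to attend 52 sessions of Weight Watchers". The BI arm gets "basic written information on self-help weight loss strategies provided by a member of the research team at the baseline visit" and weighing at follow-up, with no vouchers. The Withdrawal section recognises that uptake will vary: "Participants might choose not to attend the commercial weight loss programme, or may stop attending sessions during the trial".

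The primary model, under Clinical effectiveness in the Statistical analysis section, does not contain attendance: "The fixed effects will be intervention group, centre and baseline weight". In that section attendance appears only in descriptive summary tables.

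**The concern.** CP52 and CP12 offer the same programme for different lengths of time. Sessions attended are therefore the main route by which the longer referral could produce more weight loss. Holding sessions constant across arms compares a CP12 participant who used the whole package with a CP52 participant who used about a quarter of it (12 of 52). That takes out the contrast the trial was built to estimate. It also sets committed attenders against people who stopped early, so motivation is no longer balanced.

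A sensitivity analysis should ask the same question under different assumptions. The attendance-adjusted arm coefficient answers a different question, so neither agreement nor disagreement with the primary result says anything about robustness. The practical risk is that commissioners see an adherence-adjusted estimate that seems to overturn, or to inflate, a genuine difference between 52 and 12 weeks.

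**Working it through.** **The plan's own figures.** Inputs from the Sample size calculation and Analysis design sections: losses of 1.05, 2.7 and 4.0 kg in BI, CP12 and CP52; SD 6 kg; 200/500/500 participants; test 1 one-sided 5%, test 2 two-sided 5%.

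- Test 1: 2.3 / (6 × √(1/200 + 1/1000)) = 4.949; Φ(4.949 − 1.645) = 99.95%.
- Test 2: 1.3 / (6 × √(2/500)) = 3.426; Φ(3.426 − 1.960) = 92.87%.
- Product: 92.82%.

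All three match the article. None involves attendance, so they stand whatever is done with the Adherence clause.

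**Why adjustment moves the contrast.** Differences below are in weight change, so negative favours the arm named first. With a common slope b (kg per session, within arm):

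adjusted difference = unadjusted difference − b × (difference in mean sessions).

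The article gives no attendance figures. Assume means of about 7 of 12 in CP12 and 29 of 52 in CP52, a gap of 22 sessions. A within-arm slope of only 1.3/22 = 0.059 kg lost per session then reduces the planned CP52 minus CP12 difference to zero; a steeper one reverses it. If the covariate is the share of entitled sessions and the two CP arms have equal mean shares, the gap between them is nil and that contrast does not move. The gap between CP12 and BI is then about 7/12 = 0.58, so CP12 minus BI moves instead.

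**Simulation (assumed model).** Sessions = 12 or 52 × logistic(0.3 + 0.8 × motivation + e). Loss = 1.05 + 0.79 × sessions^0.39 + c × motivation + noise, total SD about 6. At the mean attendances, 0.79 × 7^0.39 = 1.69 and 0.79 × 29^0.39 = 2.94, close to the planned 1.65 and 2.95 kg over BI. Least squares was run with and without attendance. The SD of e sets how much attendance varies for reasons other than motivation; c is the confounding in kg per SD of motivation.

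Unadjusted, CP52 minus CP12 is about -1.26 kg (SE 0.38), and between about -1.2 and -1.3 kg across these settings. Adjusted for session count:

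| SD of e | c = 0 | c = 1 | c = 1.5 |
|---|---|---|---|
| 0 | -0.25 (SE about 0.76) | +2.7 | +4.1 |
| 1 | between -0.25 and 0 | +1.1 | +1.7 |
| 2 | about 0 | about +0.5 | about +0.8 |

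The first row makes attendance within an arm a deterministic function of motivation, so it is the extreme case for a given c.

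Adjusted for share of entitlement, CP52 minus CP12 stays at about -1.26 kg. CP12 minus BI goes from about -1.6 kg to between -0.7 and -0.6 kg with c = 0, and to as much as +4.1 kg with c = 1.5 and no other variation in attendance.

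**A second set of assumptions.** This used a square-root dose response or no effect through sessions, with CP12 attendance of about 7 to 8 sessions and CP52 of about 20 to 30:

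- No effect through sessions and no common cause: adjusting for count leaves CP52 minus CP12 at about -1.2 to -1.4 kg.
- No effect through sessions, common cause of 2 kg per SD: from -1.3 kg to between +0.1 and +1.4 kg.
- Effect through sessions and common cause of 2 kg per SD: to between +1.5 and +2.5 kg.
- Share as covariate, CP12 attending the larger share (about 7.8/12 = 65% against 20/52 = 39%), no effect through sessions, common cause of 2 kg per SD: CP52 minus CP12 is inflated from -1.3 to about -2.6 kg.

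**The case against.** The strongest reply is that the clause fixes no model. Choice of covariate and method is detail that an article can leave to an analysis plan, and the Statistical analysis section uses attendance only descriptively. The headline reversal also depends on coding attendance as a count: with share of entitlement and equal shares, CP52 minus CP12 does not move. This is fair, and it limits what can be said about size. It does not remove the point. Controlling for attendance is a stated commitment, not a gap, and either coding distorts at least one arm contrast once attendance carries some of the effect or shares a cause with weight loss.

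Three stronger readings are tempting, and the documents do not support them:

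- A reader might infer that attendance is fixed by arm. Only the free entitlement is. The Withdrawal section expects non-attendance and stopping, and nothing in the article bars BI or CP12 participants from paying to attend.
- A reader might infer that adjustment must remove or reverse the effect. It can, but it can also leave the contrast unchanged or inflate it, and the largest reversals need attendance to be driven wholly by motivation.
- A reader might infer that the primary result is at risk. The primary model omits attendance, the Discussion commits to intention to treat, and the clause is confined to sensitivity analyses.

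**Conclusion.** The concern holds in this limited form. Entering attendance in between-arm models conditions on a post-randomisation mediator whose entitlement differs by arm, and the adjusted contrast is not a robustness check on the intention-to-treat estimate. How far the result moves depends on how attendance is coded, how much of the effect it carries and how strongly it shares causes with weight loss; the article gives none of these. The kilogram figures are therefore illustrations under stated assumptions, not predictions. The slope of about 0.06 kg per session that would cancel the planned 1.3 kg difference rests only on the assumed gap of 22 sessions, and shows how little is needed. The consequence is a misleading secondary result, so the clause should be corrected, but the main conclusions do not depend on it.

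**What to change.** Reword the Adherence clause, and carry the same wording into the analysis plan:

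- Attendance and website use will be described by arm.
- Attendance may be related to weight change within an arm, labelled as an observational analysis.
- Attendance will not be a covariate in any between-arm comparison.
- CP52 against CP12 stays by intention to treat.
- If an effect of uptake is wanted, define it in advance and estimate it for each CP arm against BI with randomised arm as instrument. Define uptake as any use of the referral, meaning any session or any website use. A minimum number of sessions would strain the exclusion restriction, because people below the threshold may still benefit from some sessions or from the web access both CP arms receive. State that restriction explicitly.

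The cost is a change of wording and, if the uptake effect is kept, one extra analysis using attendance and website data. Website use needs the self-report items, because the article says only that company records of it may be available. The price of the uptake analysis is a wider interval than regression would give and an exclusion assumption that cannot be tested. Planned power stays at 99.95%, 92.87% and 92.82%.

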### Outcomes

#### Clinical effectiveness outcomes

The primary outcome will be body weight (kg) at 12 months. Secondary clinical outcomes will be: body weight (kg) at 3 and 24 months, whether a participant has lost ≥5% and ≥10% of initial body weight at 3, 12 and 24 months; waist circumference, body composition, and blood pressure at 3, 12 and 24 months; blood glucose, total cholesterol, HDL cholesterol, LDL cholesterol, and HbA1c at 12 months.

### Cost-effectiveness outcomes

The incremental cost-effectiveness ratio (ICER) of the intervention is the main outcome of the economic evaluation and will be expressed as incremental costs per incremental change in weight/BMI for the within-trial evaluation.

### Adverse events

This is a low risk trial with little reason to consider that adverse events would arise as a result of following any one of the interventions. Accordingly no formal adverse event monitoring is planned.

### Visits and measurements

Participants will attend measurement appointments at 0, 3, 12 and 24 months. Details of which measures will be taken at which appointments are summarised in Table 1.

**Table 1 T1:** Schedule of enrolment, interventions, and assessments

	**STUDY PERIOD**				
	**Enrollment**	**Baseline visit**	**Post allocation**		**Close-out**
**TIMEPOINT**	** *-t* **_ ** *1* ** _	**0**	**3 months**	**12 months**	**24 months**
**ENROLMENT:**					
**Eligibility screen**	X	X			
**Informed consent**		X			
**Allocation**		X			
**INTERVENTIONS:**					
** *Brief Intervention* **		X			
** *12 weeks Commercial Programme* **		X	X		
** *52 weeks Commercial Programme* **		X	X	X	
**ASSESSMENTS:**					
** *Height* **		X			
** *Weight* **		X	X	X	X
** *Fat mass* **		X	X	X	X
** *Waist Circumference* **		X	X	X	X
** *Blood Pressure* **		X	X	X	X
** *Blood Glucose* **		X		X	
** *Lipid Profile* **		X		X	
** *HbA1c* **		X		X	
** *DNA* **		X			
** *Demographics Questionnaire* **		X	X	X	X
** *Health Care Usage Questionnaire* **		X	X	X	X
** *EQ5D* **		X	X	X	X
** *Psychosocial Questionnaires* **		X	X	X	X
** *Intervention Usage Questionnaires* **		X	X	X	X
** *Qualitative Interviews (subset only)* **			X		

### Clinical measurements

All clinical measurements will be made in line with standardised operating procedures by trained research staff. Participants will be asked to remove shoes and heavy clothing items. Height (cm) will be measured in cm using a stadiometer. Weight and fat mass will be measured in kg using a Tanita segmental body composition analyser. Waist circumference (cm) will be measured using a tape measure, half way between the lowest rib and the iliac crest. Blood pressure will be measured using standardised methods.

### Biochemical measurements

Biochemical measurements are optional for participants and taken under separate consent. Blood samples will be taken by fully trained research staff in line with standardised operating procedures. For assessment appointments where blood will be taken (0 and 12 months), participants will be asked to attend in a fasted state (no food or drink for 12 hours prior to the appointment).

At baseline and 12 months, participants will provide a sample of whole blood for analysis of glucose, glycosylated haemoglobin (HbA1c) and lipid profile. At baseline, an additional sample of whole blood will be collected in an EDTA tube, frozen at −80 and stored for later extraction of DNA and outside the trial protocol.

### Health care usage measures

At each visit, participants will complete a Health Care Usage Questionnaire to assess their use of Health Care Services in the last 3 months.

### Psychosocial measures

Participants will complete a series of questionnaires at or before each assessment to assess psychosocial factors related to weight control.

*The Flexible and Rigid subscales if the Eating Inventory*[20] measure cognitive dietary restraint and distinguish flexible and rigid dietary restraint strategies.

The *Power of Food Scale (PFS)*[21] measures individual differences in hedonic hunger (hunger in the absence of energy need).

A visual analogue scale (VAS) will be used to assess state hunger at the time the questionnaire is completed [22]. Sensitivity analyses can examine whether this influences responses to questionnaires about eating behaviour.

*The Self-Report Habit Index (SRHI)*[23] is a measure of behavioural frequency, automaticity and identity, which has also been used to measure the automaticity of thoughts, such as body-related cognitions. In the current study, we will use this measure to examine the extent to which “watching what I eat” and “exercising regularly” become automatic and are seen as part of a participant’s identity, and the extent to which this predicts weight loss and weight loss maintenance.

*The Treatment Self-Regulation Questionnaire; Diet Self-Regulation Questionnaire (DSRQ) and Exercise Self-Regulation Questionnaire (ESRQ)* measure the extent to which a participant’s motivation to participate in treatment, eat a healthy diet, or exercise, is autonomous (i.e. they are motivated by personal reasons) or controlled (i.e. they are motivated by perceived pressure from others).

*The Problem Eating Behaviours Questionnaire (PEBQ)*[24] measures the extent to which particular eating behaviours are problematic for participants.

The *EQ5D*[15] is a self-report measure of quality of life, which will be used to calculated QALYs for the cost-effectiveness analysis.

We will measure life satisfaction using the *Satisfaction with Life Questionnaire (SLQ)*[25] and depression and anxiety using the *Hospital Anxiety and Depression Scale (HADS)*[26]*.*

### Qualitative data collection

A subset of participants from the Cambridge centre will be recruited to participate in a qualitative study. Data will be collected through semi-structured interviews with up to 15 participants in each intervention. A maximum-variation (heterogeneity) sampling technique will be used to select potential interviewees based on demographic information obtained during the telephone screening questionnaire and through a questionnaire at the baseline visit. At the 3 month visit selected participants (including some who have dropped out of treatment but not withdrawn from follow-up) will be invited to participate in an interview. Participants will be offered the choice between having the interview at their home or in a private office at the University of Cambridge. Interviews will not be held where study procedures are conducted, to reduce associations between the interview and the measurement visits of the trial in order to encourage participant’s to speak openly about their experiences of the intervention to which they have been assigned. Interviews will last approximately one hour and will follow a general topic guide that will be piloted with a subset.

### Statistical analysis

#### Analysis design

There is already good evidence to suggest that CP produces significantly greater weight loss than BI and in the event that CP is not better than BI then the comparison of the CP arms would not be of interest. Accordingly we will conduct a sequential analysis, which will preserve the Type 1 error of 5% without the need for a multiplicity correction such as Bonferroni. The sequential analysis will consist of the following 2 stages:

i) Test the one-sided hypothesis that weight loss in the CP groups combined is greater than the weight loss in the BI arm.

ii) If the first test is significant at the 5% significance level, then test the two-sided hypothesis that there is a difference between CP52 and CP12 weight loss at the 5% significance level.

### Sample size calculation

We based the power calculation on data from our previous trials [8,9] with an expected difference of 2.3 kg between BI and combined CP, 1.3 kg difference between CP12 and CP52 (for example, a weight loss of 1.05 kg in the BI arm, 2.7 kg in the CP12 arm and 4.0 kg in the CP52 arm), and an assumed standard deviation of 6 kg. The statistical testing will be performed sequentially firstly by comparing CP arms with BI and then only if significant to then test for a difference between CP12 and CP52. Power is optimised by allocating more participants to the CP arms where the smaller difference is expected. With a sample of 1200 participants allocated as 200 BI, 500 CP12 and 500 CP52, we will have 99.95% power for the first test, to detect a difference of 2.3 kg between BI and combined CP and 92.87% power to detect a difference of 1.3 kg between CP12 and CP52. The total power of the study will be 92.82%.

### Clinical effectiveness

The primary analyses will assess differences in mean weight change from baseline to 12 months between the intervention groups. In order to investigate the impact of missing data, four analysis approaches will be taken: completers only, baseline observation carried forward (BOCF), last observation carried forward (LOCF) and a missing at random (MAR) analysis using a variance components model. For the LOCF, BOCF and completers analyses, fixed effect models for continuous normal data will be fitted to the 12 month weight data. The fixed effects will be intervention group, centre and baseline weight. For the MAR analysis, a model for multivariate normal data with the same fixed effects will be fitted using measured weights at each time point using generalised least squares. Coefficient estimates and their 95% confidence intervals will be calculated for each fixed effect.

All assumptions of the models will be checked using appropriate graphs (eq a Q-Q plot of residuals to check normality, residuals versus predicted values to check homogeneity of residual variance.) If the residuals are not normally distributed then the dependent variable may be transformed to normality, if there is no such transformation then non-parametric methods will be considered.

Secondary analyses will include analyses of weight change at 3 and 24 months; changes in blood pressure, waist circumference and fat mass at 3, 12 and 24 months; changes in biochemical measures at 12 months. These will be analysed using the same regression based models. Numbers of participants in each group achieving ≥5% and ≥10% weight loss at 12 and 24 months will also be explored.

Summary tables will be produced to look at the demographic distribution of the sample (age, sex, initial weight, BMI); attendance rates; time course of attendance; website usage.

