## Background

Obesity has trebled since the 1980s and globally, excess weight is estimated to account for 44% of diabetes, 23% of ischemic heart disease and 7-41% of some cancers [1]. There is good evidence that intensive lifestyle interventions can produce weight loss linked to clinically significant health benefits [2], but such specialist interventions are costly given the high prevalence of obesity. Interventions delivered in primary care can also be demanding in terms of staff resources, set up and training and participant weight loss is often less than 5% of initial weight [3,4]. In the UK, NICE recommends consideration of any intervention that meets best practice, including referral to commercial weight loss programmes [5]. Commercial programmes are usually delivered in large groups by lay people, and preliminary evidence suggests they may be more affordable than interventions led by health professionals, making weight loss initiatives available for more individuals [6,7].

A number of commercial weight loss providers currently operate referral schemes for Public Health and the National Health Service (NHS) in the UK, whereby commissioners can purchase 12 week referral packages at a reduced cost, which are provided at no cost to patients. Two randomised controlled trials conducted by members of the current research team have demonstrated the effectiveness of commercial referrals. Jolly et al. compared a number of 12 week weight loss interventions in Birmingham’s Lighten Up service, including three commercial providers, to a control intervention (12 vouchers to attend a leisure centre) [8]. Twelve-month weight loss was significantly greater among participants referred to a commercial programme (Weight Watchers; WW) than control participants [−4.35 ± 6.9 kg vs −1.63 ± 6.0 kg; p < 0.001]. Jebb et al. [9] demonstrated that overweight and obese adults referred to this commercial programme by their primary care provider for 12 months lost twice as much weight as those who received standard care [−5.1 ± 6.1 kg vs 2.3 ± 4.2 kg; p < 0.001]. These findings suggest that referral to a commercial programme (CP) by a primary care provider is a clinically effective weight loss intervention over a one year period. However, limited data on participants who agreed to attend further follow up suggests significant weight regain beyond programme end [10].

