### Secondary objectives

#### Clinical effectiveness

We will examine differences between the three interventions in weight, waist circumference, body composition, and blood pressure at 3, 12 and 24 months and differences in biochemical measures (blood glucose, total cholesterol, HDL cholesterol, LDL cholesterol, and HbA1c) at 12 months. Specifically we will test the following hypotheses:

i) Both CP interventions achieve significantly greater weight loss than BI from baseline to 3 months and baseline to 24 months and CP52 produces significantly greater weight loss than CP12 from baseline to 24 months.

ii) Both CP interventions achieve significantly greater improvements in waist circumference, body composition and blood pressure than BI between baseline and 3, 12 and 24 months.

iii) CP52 achieves significantly greater improvements in waist circumference, body composition and blood pressure than CP12 between baseline and 3, 12 and 24 months.

iv) Both CP interventions achieve significantly greater improvements in biochemical measures than BI between baseline and 12 months, and CP52 achieves significantly greater improvements than CP12.

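### LOCF assumes no weight change after last contact, at points that sit differently against programme end in CP12 and CP52, so it is a poor check on the CP52-CP12 contrast, above all at 24 months

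*Protocol article*

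**What the plan says.** Under Statistical analysis, Clinical effectiveness, the protocol gives four approaches to missing weight: "completers only, baseline observation carried forward (BOCF), last observation carried forward (LOCF) and a missing at random (MAR) analysis". The stated purpose is "In order to investigate the impact of missing data". None of the four is named as decisive. For LOCF, BOCF and completers, "fixed effect models for continuous normal data will be fitted to the 12 month weight data". The secondary analyses, including weight change at 24 months, are covered by one sentence: "These will be analysed using the same regression based models". LOCF at 24 months is therefore implied rather than written out.

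Other sections fix the timing:

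- Visits and measurements places assessments at 0, 3, 12 and 24 months.
- Referral to a commercial provider gives CP12 vouchers for 12 sessions and CP52 vouchers for 52. In Table 1 the row "52 weeks Commercial Programme" runs to the 12-month visit; the CP12 row stops at 3 months.
- A secondary hypothesis is that "CP52 produces significantly greater weight loss than CP12 from baseline to 24 months".
- On what follows treatment, the Background says that "limited data on participants who agreed to attend further follow up suggests significant weight regain beyond programme end".
- The Discussion expects substantial incomplete follow-up but gives no figure.

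**The concern.** LOCF is unbiased only if weight stays flat after last contact, or if any later change is the same in both arms. The protocol's case for longer referral is that weight returns once a programme stops, so LOCF assumes away the process under study. It also does so at different stages in the two arms:

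| Weight carried forward | CP12 | CP52 |
|---|---|---|
| 3 months | about the end of the programme | early, on programme |
| 12 months | about 9 months after the programme | about the end of the programme |

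The 24-month comparison matters most. A participant last seen at 12 months enters that analysis with a CP52 weight from which later regain is missing, set against a CP12 weight that already contains some months of regain. The 12-month contrast is in effect used again for that participant. At stake is whether an apparent 2-year benefit of the longer referral could partly reflect the imputation rule.

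**Working it through.** **Inputs.** From Sample size calculation: a CP52-CP12 difference of 1.3 kg at 12 months (losses of 4.0 and 2.7 kg), SD 6 kg, 200 BI, 500 CP12 and 500 CP52. From Analysis design: test 1 one-sided 5%, test 2 two-sided 5%. Assumed here, because the protocol gives no values: the dropout shares, the true 24-month difference D, and a 3-month CP52-CP12 difference of zero. The last is reasonable because the arms differ in length and not in content. SD is held at 6 kg throughout.

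**Step 1: reproduce the stated power** (normal approximation).

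- Test 1: SE = 6 × √(1/200 + 1/1000) = 0.465; 2.3/0.465 − 1.645 gives 99.95%.
- Test 2: SE = 6 × √(2/500) = 0.379; 1.3/0.379 − 1.96 gives 92.87%.
- Product: 92.82%.

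All three agree with the protocol.

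**Step 2: 24 months.** Let m3 be the share last seen at 3 months or earlier and m12 the share last seen at 12 months, equal in both arms. Then

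LOCF difference = (1 − m3 − m12) × D + m12 × 1.3 + m3 × 0.

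With D = 0 this is 1.3 × m12, whatever m3 is. The probability of rejection is Φ(δ/0.379 − 1.96) + Φ(−δ/0.379 − 1.96), where δ is the LOCF difference.

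| m12 | LOCF difference when D = 0 | Rejection (nominal 5%) |
|---|---|---|
| 10% | 0.13 kg | 6.4% |
| 20% | 0.26 kg | 10.5% |
| 30% | 0.39 kg | 17.7% |

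In the same setting BOCF expects (1 − m3 − m12) × 0 + (m3 + m12) × 0 = 0, so this false signal comes from LOCF and not from single imputation in general.

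**Step 3: when a real 24-month benefit exists.** LOCF difference − D = 1.3 × m12 − (m3 + m12) × D. LOCF inflates only if D < 1.3 × m12/(m3 + m12). That threshold is 0.65 kg when m3 = m12, and 0.43 kg when m3 = 20% and m12 = 10%. Above it LOCF understates. With D = 1.0 kg, m3 = 30% and m12 = 10%, it gives 0.60 × 1.0 + 0.10 × 1.3 = 0.73 kg.

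**Step 4: 12 months.** Let a share d in each arm be last seen at 3 months, and let the planned effect hold in those lost. LOCF expects (1 − d) × 1.3.

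| d | LOCF difference | Power, LOCF | Power, completers with 1.3 kg |
|---|---|---|---|
| 10% | 1.17 kg | 86.9% | 90.2% |
| 20% | 1.04 kg | 78.2% | 86.5% |
| 30% | 0.91 kg | 66.9% | 81.8% |
| 40% | 0.78 kg | 53.8% | 75.6% |

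BOCF also assigns these participants a difference of zero and so expects the same (1 − d) × 1.3.

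Unequal dropout changes the result:

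- 40% lost in CP12, 20% in CP52, common 3-month loss 3.5 kg: (0.8 × 4.0 + 0.2 × 3.5) − (0.6 × 2.7 + 0.4 × 3.5) = 3.90 − 3.02 = 0.88 kg.
- 20% lost in CP12, 40% in CP52, common 3-month loss 6 kg: (0.6 × 4.0 + 0.4 × 6) − (0.8 × 2.7 + 0.2 × 6) = 4.80 − 3.36 = 1.44 kg, above the planned 1.3.

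**The case against.** The strongest reply is that LOCF is one of four approaches, reported to show how far the answer depends on missing data, with a MAR model using all measured weights beside it. Nothing says that a conclusion rests on LOCF alone. LOCF at 24 months has to be inferred. Participants who stop the intervention are still followed up, and the Withdrawal section asks non-attenders for a self-measured weight for use in sensitivity analyses. All of this stands and limits the weight of the point.

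A reader might go further and infer three things that the documents do not support.

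- *That LOCF generally creates a sustained CP52 benefit.* Step 3 shows inflation only below a threshold in D; above it LOCF understates. The average artefact in Step 2 is also below the 0.74 kg (1.96 × 0.379) needed for significance. That does not remove the problem, because the rejection rate still rises to two to three and a half times nominal when m12 is 20% to 30%.
- *That LOCF necessarily hides a real difference at 12 months because of the arm-specific timing.* The dilution in Step 4 is generic and shared with BOCF. It disappears if those lost had also stopped attending and truly differ by nothing, and it can reverse. Where it does occur, it is conservative for a claim that CP52 is better.
- *That the bias has one sign at 12 months and the opposite sign at 24.* At both times the sign depends on who is lost, when, and what the true difference is.

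The detail of a delta adjustment may properly sit in the analysis plan, which is not shown. The choice of LOCF, however, is made in the protocol.

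**Conclusion.** The point holds as a conditional weakness in a chosen method. LOCF rests on an assumption that the protocol's own account of regain contradicts, and the carried weights sit at different stages of treatment in the two arms being compared.

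The firmest consequence is at 24 months. If the planned 1.3 kg is present at 12 months in those later lost and the true 24-month difference is zero, the two-sided 5% test rejects about 10.5% or 17.7% of the time with 20% or 30% last seen at 12 months. The result does not depend on how many were lost earlier, given no 3-month difference. It does rest on assumed dropout shares, equal in both arms, and a constant SD of 6 kg.

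At 12 months the evidence supports only possible dilution, of the same size as under BOCF. Since the direction of LOCF's bias cannot be known in advance, agreement between LOCF and the other analyses would say little about the duration question. This is a cheap improvement worth making; it does not show that the trial's conclusion would be wrong.

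**What to change.** In the Clinical effectiveness analysis section, remove LOCF from the CP52-CP12 contrasts at 12 and 24 months. Replace it with a sensitivity analysis that departs from MAR by a stated amount: impute under the MAR model, shift the imputed weights after last contact by a delta, and vary delta over a stated range separately by arm. The self-measured weights requested under Withdrawal can help to set that range.

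If LOCF is kept for reporting, the minimum is a sentence saying that no conclusion about sustained 24-month benefit will rest on a carried-forward weight. The section should also say outright which approaches apply at 24 months.

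The cost is a change of wording and one replacement analysis, with no new data. The downside is some loss of comparability with earlier weight-loss trials that reported LOCF.
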